# **Effect of photobiomodulation treatment in the sublingual, radial artery region, and along the spinal column in individuals with multiple sclerosis: Protocol for a randomized, controlled, double-blind, clinical trial**

## **Abstract**

**Background:** Multiple sclerosis (MS) is an autoimmune disease, for which the forms of treatment are medication and rehabilitation. However, *in vitro* and *in vivo* studies have demonstrated that photobiomodulation can be an effective treatment modality for inflammatory diseases, including MS. Photobiomodulation has a broad range of benefits, such as the avoidance of cell and tissue death, the stimulation of healing and injury repair, reductions in pain, edema and inflammation, cell proliferation and even apoptosis. The outcomes of photobiomodulation include the regeneration of cells, the stimulation of the growth of Schwann cells, a reduction in spasticity, functional improvements, a reduction in nitric oxide levels and the upregulation of the cytokine IL10, demonstrating that this therapeutic modality can offer neuro-protection.

**Methods:** A randomized, controlled, double-blind, clinical trial is proposed. The patients will be divided into 6 groups. Groups 1 and 2 will receive sham and active photobiomodulation in the sublingual region, respectively. Groups 3 and 4 will receive sham and active photobiomodulation along the spinal cord, respectively. Group 5 will receive placebo treatment with photobiomodulation on the skin in the region of the radial artery with a specific bracelet. Group 6 will be treated with photobiomodulation on the skin in the region of the radial artery.

**Discussion:** Treatment for MS is directed at the immune response and slowing the progression of the disease. This is one of the first clinical trials involving photobiomodulation in the sublingual region and along the spinal cord, which could help establish a promising new form of non-pharmacological treatment for autoimmune diseases. This is one of the first clinical trials with sublingual photobiomodulation and along

the spinal cord that could help establish a new form of promising treatment of the disease associated with pharmacological treatment.

**Key words:** Low-level laser therapy, photobiomodulation, multiple sclerosis, oxidative stress, physical therapy.

## 1. Introduction

Multiple sclerosis (MS) is an demyelinating, neurodegenerative, inflammatory disorder of the central nervous system (CNS) characterized by the selective destruction of the myelin sheath.[1,2] MS has a complex, multifactor etiology that is not fully understood, but it is believed that the formation of demyelinating lesions may be due to autoimmune processes as well as environmental and genetic factors.[3,4]

Inflammation of the CNS is an important mechanism that contributes to demyelination and neurodegeneration. Th1, Th17, and B cells are activated in peripheral regions, pass through the blood–brain barrier, and interact with antigen-presenting cells (astrocytes, microglia, macrophages, and dendritic cells), inducing the production of proinflammatory cytokines and oxidative stress.[5,6] B lymphocytes serve as specific antigen-presenting cells for T cells and produce specific antibodies for myelin antigens, making myelin the target of immune cells that mistake it for a foreign antigen.[6,7]

Oxidative stress occurs due to the accumulation of free radicals (reactive oxygen and nitrogen species),[8] which leads to inflammation, oligodendrocyte damage, abnormalities in synaptic transmissions, axonal degeneration, and neuronal death, suggesting that oxidative stress is an important factor in neurodegeneration.[9,10] Myelin and oligodendrocyte damage caused by inflammation gives rise to a multitude of symptoms, such as sensory alterations, fatigue, physical and/or mental disability, balance disorders, spasticity, muscle weakness, urinary incontinence, cognitive impairment, neuropathic pain, and visual deficiency.[1,3]

This disease occurs in different forms, such as relapsing–remitting MS, which is characterized by sudden-onset short-term or long-term relapses, secondary progressive MS, which has a progressive course that results in severe, irreversible disability, and primary progressive MS, which is a progressive type with no relapses or periods of remission.[1,11,12]

Prognosis is unpredictable with regard to the disability that occurs due to the manifestations of the disease, which are normally associated with progressive locomotion impairment.[12] Treatment is directed at the immune response and slowing the progression of the disease, which can be achieved with the use of drugs.[12,13] Moreover, rehabilitation can lead to improvements in walking capacity, cognition, fatigue, depression, quality of life, participation in activities, muscle strength, cardiovascular performance, and balance.[13,14]

In vitro and in vivo studies have demonstrated that photobiomodulation is effective for inflammatory diseases, including MS.[15] This therapeutic modality has a broad range of benefits, such as the avoidance of cell and tissue death, the stimulation of healing and injury repair, reductions in pain, edema and inflammation, cell proliferation, and even apoptosis.[15,16] The outcomes of photobiomodulation include the regeneration of

cells, the stimulation of the growth of Schwann cells, a reduction in spasticity, functional improvements, a reduction in nitric oxide levels, and the upregulation of the cytokine IL10, demonstrating that this therapeutic modality can offer neuroprotection.[15,17]

The aim of the proposed study is to evaluate whether photobiomodulation in the sublingual region and along the spinal cord modulates the expression of IL-10, TNF- $\alpha$ , and nitric oxide in individuals with MS. The main objective of this study is to evaluate if the photobiomodulation along the spinal cord in the sublingual region and irradiation in the radial artery can modulate the expression of IL-10, TNF- $\alpha$ , and nitric oxide.

## **Methods/Design**

### **Trial design**

A controlled, clinical trial is proposed, which will follow the guidelines for research involving human subjects stipulated in Resolution 466/2012 of the Brazilian National Board of Health and will be submitted for approval from the Human Research Ethics Committee of University Nove de Julho. The participants or their legal guardians will sign statements of informed consent authorizing participation in the study (APPENDIX 1).

Inclusion criteria: Diagnosis of MS, age between 18 and 60 years, currently undergoing pharmacological treatment, capable of understanding and following verbal instructions and score of < 7 on the Expanded Disability Status Scale. No restriction will be imposed regarding gender.

Exclusion criteria: other autoimmune disease and/or tumor, relapse of disease activity during treatment, and not undergoing pharmacological treatment. Other autoimmune diseases; Neoplasias, Heart failure, Respiratory failure, Renal insufficiency, Hepatic insufficiency, Acquired immunodeficiency syndrome, Patients with relapses of the disease.

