### **Recruitment and randomization**

Patients will be recruited from the Integrated Health Clinic of University (Vergueiro, Memorial and Vila Maria campuses). Patients with a diagnosis of MS will be screened for the eligibility criteria through telephone interviews. Selected individuals with a signed statement of informed consent will be randomized. Randomization will be performed in blocks. Groups 1 and 2 will receive sham and active photobiomodulation in the sublingual region, respectively. Groups 3 and 4 will receive sham and active photobiomodulation along the spinal cord, respectively. Group 5 will receive placebo treatment with photobiomodulation on the skin in the region of the radial artery with a specific bracelet. Group 6 will be treated with photobiomodulation on the skin in the region of the radial artery. The participants will not be deprived of any medication for the treatment of the

base condition. Randomization will be stratified by clinic using block allocation tables to ensure equal proportions in the distribution of treatments. The participants and evaluator will be blinded to the allocation.

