## **Evaluations**

### **EDSS**

The participants will be evaluated before and after treatment using the Expanded Disability Status Scale administered by a physiotherapist (approximate application time: 15 minutes).

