## **Treatment**

The participant will be placed on an examining table in a comfortable position. Both the operator and participant will use eye protection. Transcutaneous irradiation of the spinal cord will be performed on segments corresponding to the nerve roots of the lumbosacral plexus (T12-S5) and cervicothoracic plexus (C5-T1-2). Twenty points will be irradiated for 90seconds (total treatment time: 1800seconds). In the group submitted to sublingual irradiation, disposable plastic wrap will cover the application pen for the purposes of hygiene, (total treatment time: 360seconds). In the group submitted photobiomodulation on the skin in the region of the radial (total treatment time: 360seconds). The treatment will be performed twice a week totaling 24 consecutive weeks and after 3 months of treatment the patients will be submitted to reassessment of all complementary tests that have been requested, cytokines, nitric oxide, and EDSS.

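### An exclusion criterion for relapse during treatment, on its natural reading, removes patients after randomisation and can bias the active-sham comparison if treatment alters relapse

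*Protocol*

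**What the plan says.** The exclusion criteria under Trial design come as two consecutive lists. The first includes "relapse of disease activity during treatment, and not undergoing pharmacological treatment". The second ends with "Patients with relapses of the disease" and gives no time window.

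Recruitment and randomization puts eligibility screening, by telephone, before allocation: "Selected individuals with a signed statement of informed consent will be randomized". The Abstract states that "The patients will be divided into 6 groups", which form three sham/active pairs. Under Treatment, "The treatment will be performed twice a week totaling 24 consecutive weeks", and a reassessment of cytokines, nitric oxide and EDSS is scheduled. The EDSS section says: "The participants will be evaluated before and after treatment using the Expanded Disability Status Scale".

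The Introduction holds that "photobiomodulation is effective for inflammatory diseases, including MS", and its stated aims are effects on IL-10, TNF-alpha and nitric oxide. The protocol does not say whether a patient who relapses after allocation stays in follow-up.

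**The concern.** An eligibility criterion should be decidable before allocation. A relapse during study treatment can be seen only afterwards, so following this criterion means dropping randomised patients.

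The dropping would not be neutral. The Introduction describes MS as an inflammatory disease in which cytokines and oxidative stress do the damage, and it expects photobiomodulation to act on that process. A relapse is therefore plausibly linked to the outcomes and, if the treatment works or harms, to the arm as well. If active treatment prevents relapse, the sham arm loses more of its most inflamed patients and the benefit is understated. If active treatment provokes relapse, the patients who would show the harm are the ones removed.

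**Working it through.** **1. Which treatment is meant?**

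- For photobiomodulation: the same sentence calls background therapy pharmacological treatment. In the EDSS and Treatment sections the unqualified word means photobiomodulation.
- For background drugs: the only treatment named in the eligibility text is pharmacological, and the criteria are applied at screening.
- The separate relapse item in the second list does not settle it. That list largely repeats the first (autoimmune disease and tumours appear in both), so the item may only restate the earlier one.

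The first reading is the natural one; the second is not excluded. The steps below apply to the first.

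**2. Patients per arm.** The protocol gives no figure for relapse, so there is none to reproduce on that point. Its sample size (32 individuals, effect size 0.8, power 0.9566) matters only for arm size. One-way ANOVA power with noncentrality f² × N = 0.64 × 32 = 20.48 and alpha 0.05 gives:

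- 4 groups: 0.9566, an exact match
- 6 groups: 0.9026

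Whether 32 is the six-group total is not stated. If it is, 32/6 = 5.3, so arms hold 5 or 6 patients and one removal costs 1/6 = 17% to 1/5 = 20% of an arm. With four groups, 32/4 = 8 and one removal costs 1/8 = 12.5%.

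**3. Attenuation when relapse depends on the marker (all inputs assumed).** Let the marker Y be N(0, 1) on sham and N(−0.8, 1) on active, with logit P(relapse) = logit(base) + slope × Y. The table shows the active-minus-sham difference among non-relapsers, by numerical integration. In all randomised patients it is −0.80.

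| Base | Slope | Sham relapse | Active relapse | Difference | Attenuation |
|---|---|---|---|---|---|
| 0.1 | 0.25 | 10% | 9% | −0.796 | 0.5% |
| 0.3 | 0.5 | 31% | 23% | −0.765 | 4.4% |
| 0.1 | 1 | 13% | 7% | −0.745 | 7% |
| 0.3 | 1 | 33% | 20% | −0.696 | 13% |
| 0.1 | 2 | 20% | 8% | −0.649 | 19% |
| 0.3 | 2 | 37% | 18% | −0.578 | 28% |

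Attenuation is 1 − difference/(−0.80); for the last row, 1 − 0.578/0.80 = 28%. Slopes of 0.25, 0.5, 1 and 2 are odds ratios per SD of e^0.25 = 1.3, e^0.5 = 1.6, e^1 = 2.7 and e^2 = 7.4.

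**4. Cross-check with a second model (also assumed).** Relapse occurs when a latent score, correlated ρ with the marker, passes a threshold c set by the relapse risk p. Deleting relapsers lowers an arm's mean by ρ × φ(c)/(1 − p). The shift in the active-sham difference is ρ times the gap between arms:

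- 15% sham, 5% active: gap 0.274 − 0.109 = 0.166; shift 0.05 (ρ = 0.3) to 0.12 SD (ρ = 0.7)
- 20%, 10%: gap 0.350 − 0.195 = 0.155; shift 0.05 to 0.11 SD
- 30%, 15%: gap 0.497 − 0.274 = 0.222; shift 0.07 to 0.16 SD

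The shift changes sign if the two risks are exchanged.

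**5. No effect of treatment on relapse.** With equal risks, and the same link between relapse and marker in both arms, the shift is zero in the second model. Centring Y on each arm's own mean in the first model equalises the risks there, and the difference returns to −0.80.

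**The case against.** The strongest reply is that the criterion may be a baseline one: relapse while on background drugs, judged at telephone screening. That cannot be dismissed, and under it nobody is removed after randomisation for relapse. What remains then is ambiguous wording that staff at three campuses could apply in two ways.

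A second reply is that analysis sets and the handling of events after randomisation are commonly left to a SAP, which is not shown. That is fair for the analysis set. Eligibility, however, is fixed in the protocol, and no SAP can restore blood samples and EDSS scores never collected from excluded patients.

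A third is that the bias is small beside the noise. With 5.3 patients per arm the standard error of a difference is √(2/5.3) = 0.61 SD, against a largest illustrated shift of 0.80 − 0.58 = 0.22 SD. Under the trial's own hypothesis the error is also conservative. Both points stand for the marker comparison. Neither covers the case where treatment provokes relapse and the criterion hides it.

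A reader might also infer that "Patients with relapses of the disease" bars everyone with relapsing-remitting MS. The text does not support that. The Introduction names that form explicitly when it means it, and the phrase more naturally describes patients in relapse. The strict reading would also leave few relapses to remove, which sits badly with the bias argument. The supportable point is only that the time window is missing.

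**Conclusion.** The point holds conditionally. On the natural reading, the protocol excludes randomised patients for an event related to its outcomes, which can bias the active-sham comparison or conceal harm if photobiomodulation alters relapse. On the baseline reading, which the wording leaves open, there is no such bias.

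A reader might go further and conclude that the comparison is certainly biased, or that the effect will be understated by as much as 28%. The documents support neither. They give no relapse rate and no association between relapse and the markers. The upper figure needs 37% sham relapse and an odds ratio of 7.4 per SD together; a weak association gives under 1% at low relapse risk, and no effect of treatment on relapse gives about zero. The cost of each removal (17% to 20% of an arm, or 12.5%) depends on whether 32 is the total over six groups or corresponds to four groups of 8.

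**What to change.** - Limit the exclusion criteria to facts known before randomisation: delete the words that refer to the treatment period from the first relapse criterion, and state the time window meant by "Patients with relapses of the disease".
- State that every randomised patient stays in the assigned arm, and that the blood sample and EDSS already scheduled are still collected after a relapse.
- Report relapses by arm.

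This is a change of wording that uses visits already planned. Its cost is some added variance in the biomarkers from patients who relapse. Whether study treatment continues after a relapse is a clinical matter and is not addressed here.

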### **Recruitment and randomization**

Patients will be recruited from the Integrated Health Clinic of University (Vergueiro, Memorial and Vila Maria campuses). Patients with a diagnosis of MS will be screened for the eligibility criteria through telephone interviews. Selected individuals with a signed statement of informed consent will be randomized. Randomization will be performed in blocks. Groups 1 and 2 will receive sham and active photobiomodulation in the sublingual region, respectively. Groups 3 and 4 will receive sham and active photobiomodulation along the spinal cord, respectively. Group 5 will receive placebo treatment with photobiomodulation on the skin in the region of the radial artery with a specific bracelet. Group 6 will be treated with photobiomodulation on the skin in the region of the radial artery. The participants will not be deprived of any medication for the treatment of the

base condition. Randomization will be stratified by clinic using block allocation tables to ensure equal proportions in the distribution of treatments. The participants and evaluator will be blinded to the allocation.

## **Evaluations**

### **EDSS**

The participants will be evaluated before and after treatment using the Expanded Disability Status Scale administered by a physiotherapist (approximate application time: 15 minutes).

### **Blood collection for analyzes of inflammation, oxidative stress**

All participants will go through a medical consultation at the UNINOVE clinic, to confirm the diagnosis of MS, and after which it will be collected by a nurse blood samples (10 ml) will also be taken for the determination of IL-10 (anti-inflammatory), TNF alpha and nitric oxide (proinflammatory). The evaluation of these cytokines will be through ELISA and griess reaction.

## **Treatment**

The participant will be placed on an examining table in a comfortable position. Both the operator and participant will use eye protection. Transcutaneous irradiation of the spinal cord will be performed on segments corresponding to the nerve roots of the lumbosacral plexus (T12-S5) and cervicothoracic plexus (C5-T1-2). Twenty points will be irradiated for 90seconds (total treatment time: 1800seconds). In the group submitted to sublingual irradiation, disposable plastic wrap will cover the application pen for the purposes of hygiene, (total treatment time: 360seconds). In the group submitted photobiomodulation on the skin in the region of the radial (total treatment time: 360seconds). The treatment will be performed twice a week totaling 24 consecutive weeks and after 3 months of treatment the patients will be submitted to reassessment of all complementary tests that have been requested, cytokines, nitric oxide, and EDSS.

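### The Treatment section sets a 24-week course but schedules the only follow-up of the main outcomes after 3 months of treatment, about half-way through if taken at its word

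*Protocol*

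**What the plan says.** Course length and reassessment time appear in one sentence of the protocol's Treatment section: sessions are given "twice a week totaling 24 consecutive weeks and after 3 months of treatment the patients will be submitted to reassessment". The reassessment covers the cytokines, nitric oxide and EDSS, along with the other tests requested.

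Four other places bear on the schedule:

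- **Blood collection section.** It describes the draw linked to the consultation that confirms the diagnosis: "after which it will be collected by a nurse blood samples (10 ml) will also be taken". It gives no later sampling time.
- **EDSS section.** "The participants will be evaluated before and after treatment using the Expanded Disability Status Scale". The Treatment section puts EDSS in the same reassessment as the blood markers.
- **Introduction.** The main objective is whether irradiation at the three sites "can modulate the expression of IL-10, TNF"-alpha and nitric oxide.
- **Trial design.** One exclusion criterion is "relapse of disease activity during treatment", so its window depends on how long treatment lasts.

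No section states a total number of sessions or names an assessment week.

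**The concern.** The two halves of the sentence do not fit together. A 24-week course lasts well beyond 3 months, so a reassessment made after 3 months of treatment comes while sessions are still being given. It is also the only follow-up blood sample scheduled. The effect of the full course on the main outcomes would then go unmeasured, while participants attended roughly another three months of sessions with no marker reading after them.

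The schedule is the same in every arm, so this does not bias active against sham and does not change the type I error. What is at stake is which exposure the result describes: half of the course, all of it, or all of it plus a treatment-free interval. If staff interpret the sentence differently, the number of sessions received and the week of assessment could also vary between participants.

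**Working it through.** **Inputs.** From the Treatment section: 2 sessions per week, 24 weeks, reassessment at 3 months. The protocol does not define a month, so two conventions are used: 4 weeks, and a calendar month of 30.4375 days. The protocol gives no session count or assessment week to reproduce, and its sample-size figures do not enter.

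**Course as written**

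- Sessions: 24 × 2 = 48.
- Length: 24 × 7 / 30.4375 = 5.5 months.

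**Position of the 3-month reassessment in that course**

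| | 4-week months | Calendar months |
|---|---|---|
| Week of reassessment | 3 × 4 = 12 | 3 × 30.4375 / 7 = 13.0 |
| Sessions given by then | 12 × 2 = 24 | 13 × 2 = 26 |
| Share of the course | 24 / 48 = 50.0% | 26 / 48 = 54.2% |
| Sessions still to come | 48 − 24 = 24 (50.0%) | 48 − 26 = 22 (45.8%) |
| Weeks still to come | 24 − 12 = 12 | 24 − 13 = 11 |

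**Three possible readings**

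| Reading | Course | Reassessment | Sessions before it | End-of-course blood sample |
|---|---|---|---|---|
| As written | 48 sessions, 24 weeks | Week 12–13 | 24–26 | None |
| 24 was meant as sessions | 24 / 2 = 12 weeks (12 × 7 / 30.4375 = 2.8 months) | About week 12 | 24 | Yes |
| Visit 3 months after the course | 48 sessions, 24 weeks | 24 + 12 = week 36 to 24 + 13 = week 37 | 48 | None |

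**Check against the other sections.** The first reading can be carried out, but an EDSS at week 12–13 of 24 is not an assessment after treatment, so it conflicts with the EDSS section. The second agrees with the EDSS section and with 3 months of treatment, but requires replacing the stated unit: the text says weeks, and consecutive ones. The third agrees with the EDSS section but requires reordering the words, since the text counts months of treatment rather than months since treatment. No section settles the choice.

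**Relapse exclusion.** The window for relapse during treatment is 24 weeks as written and 12 weeks under the second reading.

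**The case against.** The strongest reply is that this is a slip of the pen. Twice a week with a total of 24 sounds like a session count; 24 sessions take 12 weeks, which is about 3 months, and the reassessment then falls at the end of the course, as the EDSS section implies. On that view no sample is missing, and a headline about mid-course measurement rests on the reading that fits the rest of the document least well. It can be added that a randomised comparison at 3 months is valid in itself, that the main objective names no time point, that the range from week 12 to week 37 spans mutually exclusive readings rather than variation within one trial, and that the relapse exclusion has wording problems of its own.

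Much of this stands. The 24-session reading is plausible, and the protocol does not show that anyone chose a mid-course measurement. The 50–54% figure holds only for the schedule as written. Inconsistent execution by staff is a risk, not an established fact. The relapse window is a secondary matter, because the same list also excludes patients with relapses without giving any window.

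The objection does not remove the defect. If 24 sessions were intended, the protocol prescribes twice the intended course, and staff who follow it would deliver 48. If a post-course visit was intended, the wording is wrong and there is still no end-of-course sample. Each reading therefore calls for a correction. Nor can this be left to a statistical analysis plan, which is not at hand: session numbers and blood-draw times are carried out from the protocol, and an analysis plan cannot supply a sample that was never taken.

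**Conclusion.** The concern holds: the schedule is wrong as written. Followed word for word, it places the only post-baseline measurement of IL-10, TNF-alpha and nitric oxide at week 12–13, after 24–26 of 48 sessions (50–54%), and leaves 22–24 sessions over the next 11–12 weeks with no blood sample after them. If a different course or visit was intended, the text misstates the course length or the assessment time.

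Confidence is high that the stated course length and reassessment time do not match and that no section reconciles them. Which reading was intended cannot be determined from the protocol. The fault does not invalidate the active-versus-sham comparison, but it leaves undefined the exposure behind the main result. It should be fixed before treatment starts, because an end-of-course sample that was not drawn cannot be recovered.

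**What to change.** Rewrite the sentence in the Treatment section to give one number of sessions, one course length in weeks and one named reassessment week at the end of the course. Two consistent versions are:

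- 48 sessions over 24 weeks, with reassessment at the end of week 24; or
- 24 sessions over 12 weeks, with reassessment at the end of week 12.

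The clinical team decides which course is intended. Use the same week for the blood markers and EDSS in all six arms, and bring the EDSS section into line. If a 3-month sample during a 24-week course, or a visit 3 months after it, is also wanted, list it as an additional time point.

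The cost is one sentence and one matching edit. If the 24-week course stands and the 3-month sample is kept as well, add one 10 ml blood draw, its assays and one EDSS per participant at week 24.
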